### Statistical analysis

The EHA and EC pCR rates and 95% CIs will be calculated for both groups. Patient’s quality of life will be assessed at baseline, week 1, and at 3, 6, 9, 12, 18, and 24 months. Other data acquisition and analyses will include the complete response rate for the trial treatment period; the rate of trial continuation for the LNG-IUD plus metformin and MA plus metformin groups; BMI values and homeostatic model assessment of insulin resistance (HOMA-IR) results of all response cases that wish to become pregnant; the proportion of patients that become pregnant at least once during the trial period; pregnancy outcomes (miscarriage, stillbirth, live birth, and weeks of gestation); and the proportion of patients that give birth to a child. Data will be reported as mean and standard deviation (SD), median and interquartile range (IQR), or number and percentage (%) based on if the data are continuous or categorical and on the normality assumption. The Kolmogorov–Smirnov normality test will be used to check the normality of continuous variables. For comparisons between 2 groups, Student’s t-test or the Mann–Whitney U test will be used according to the normality assumption. The Chi-square test will be used to compare the number of cases and percentage between groups.

This study will also investigate changes in the expression of molecular biomarkers. Since the changing results over time are repeated measurements, statistical tests of dependent data, such as the paired t-test or mixed-design ANOVA will be used.

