### Study assessments and procedures

The study assessments and procedures performed at baseline and 3, 6, 9, 12, 18, and 24 months are summarized in Table 1.

**Table 1 Tab1:** Schedule of patient assessments

	Baseline	Day 1	3 months (± 14 days)	6 months (± 14 days)	9 months (± 14 days)	12 months (± 14 days)	18 months (± 14 days)	24 months (± 14 days)
Assessment								
Informed consent	√							
CT of pelvis/abdomen^a^	√			√		√	√	√
CT chest (or chest X-ray)	√			√		√	√	√
MRI of pelvis	√			√		√	√	√
Pelvic ultrasonography^b^	√		√	√	√	√	√	√
CA125	√		√	√	√	√	√	√
FBG (fasting blood-glucose)	√		√	√	√	√	√	√
Serum or urine pregnancy test	√	√(urine)						
Fasting blood sugar	√		√	√	√	√	√	√
HbA1c	√		√	√	√	√	√	√
HE4 (human epididymal protein4)	√		√	√	√	√	√	√
Blood collection for biomarkers and genetic testing	√							
ERα, PRα and PRβ (estrogen receptor, progesterone receptor)								
Medical history	√							
Concomitant medications	√		√	√	√	√	√	√
ECOG	√		√	√	√	√	√	√
Height	√							
Weight	√		√	√	√	√	√	√
BMI	√		√	√	√	√	√	√
Surgical, medical, gynecologic, and family history	√							
Self-efficacy and social support questionnaire	√		√	√	√	√	√	√
Adverse events			√	√	√	√	√	√
Hysteroscopy, D&C			√	√	√	√	√	√
Intervention adherence			√	√	√	√	√	√

*BMI* body mass index, *CA125* cancer antigen 125, *CT* computed tomography, *D&C* dilation and curettage, *ECOG* Eastern Cooperative Oncology Group, *HbA1c* glycosylated hemoglobin, *MRI* magnetic resonance imaging

^a^CT scans will be performed every 6 months. However, if the ultrasound shows obvious lesions in the uterine cavity and tissue pathological examination indicates no remission or the disease has progressed, additional CT examination will be performed

^b^Patients will receive pelvic ultrasonography and hysteroscopic and curettage every 3 months for endometrial pathological examination. If the ultrasound shows obvious lesions in the uterine cavity and tissue pathological examination indicates no remission or the disease has progressed, additional CT/MRI examination will be performed

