### Interventions

The LNG-IUD is approved for contraception, treatment of idiopathic menorrhagia, and prevention of endometrial hyperplasia. The most common adverse reactions are uterine/vaginal bleeding alterations, amenorrhea, intermenstrual bleeding and spotting, abdominal/pelvic pain, and ovarian cysts. The device is prohibited for use in women with known or suspected pregnancy, congenital abnormal uterine development, breast cancer, unexplained vaginal bleeding, reproductive tract infection, and other conditions.

Systemic progestogen therapy, such as MA 160 mg orally once a day, is effective for the treatment of hormone-sensitive hyperplasia and tumors [32]. However, PRs are often downregulated leading to a relatively short duration of effectiveness [33]. In addition, systemic therapy is associated with low compliance rates due to adverse effects including nausea, thromboembolic complications such as deep vein thrombosis (DVT), pulmonary embolism (PE), stroke, weight gain, abnormal vaginal bleeding, and increased risk of breast cancer [34].

Study participants will be instructed to take metformin with meals, 1000 mg daily. This dose is similar to that used in clinical trials as an adjuvant breast cancer treatment (NCT00909506 and NCT01302002), ranging from 500 to 1000 mg daily. Metformin is well-tolerated by the vast majority of patients with no significant side effects. The gastrointestinal adverse effects of metformin are dose-dependent [35]. The dose of 1000 mg daily can be reduced to 500 mg daily if needed. Metformin is associated with abdominal pain, diarrhea, lactic acidosis, nausea and vomiting, and taste changes [35]. Metformin decreases absorption of vitamins B9 and B12, in turn elevating homocysteine levels. Metformin is not used for patients with moderate or worse renal function impairment.

Because all participants in the trial will be obese, a weight loss program will be implemented. The weight loss program is an evidence-based and tested diet and exercise intervention program that has led to weight loss success in obses people [36]. Exercise levels (sedentary, moderately active, and sufficiently active) will be measured using the Active Australia Survey [37].

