### Baseline assessments

Baseline assessments will be performed according to the trial standard operating procedure (SOP), including medical history, determination of BMI, CT and MRI imaging, blood tests including tumor marker CA125. Endometrial tissue specimens will be obtained by treating gynecologic oncologists via hysteroscopy and D&C. Histopathological examination of tissue specimens will confirm the cell type and grade of differentiation. Histopathological specimens will also be used for pathological molecular typing.

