Matsuo et al. reported that for patients with endometrial dysplasia, concurrent metformin administration was associated with an improved response in women using the LNG-IUD as compared with those receiving metformin plus progesterone (oral progesterone/LNG-IUD) treatment [43].

This proposed trial has strengths and weaknesses. A marked strength is that no high-quality studies are comparing the efficacy of an LNG-IUD plus metformin or MA plus metformin in the treatment of early EC. In other relevant studies, the primary endpoint is the pathological response rate while in the proposed trial the endpoints will be the pCR rate, pregnancy outcomes, and recurrence rates. The proposed trial is to investigate whether metformin combined with local progesterone and systemic progesterone have different therapeutic effects on endometrial lesions and whether there are different pathways for their “sensitization” effects. Finally, in ongoing trials (NCT01594879, NCT01943058, NCT02035787, NCT04792749, NCT02065687, NCT01968317, NCT01697566), metformin is administered in combination with progestin, and is discontinued after remission. In these trials, only an anticancer effect of metformin is expected as an outcome. Since most of the participants of this trial will be obese, they are likely to develop insulin resistance and abnormal glucose metabolism. Thus, this trial will also evaluate the expected improvements in the metabolic profile following the addition of metformin. Strengths of our work also include its prospective design, standardized treatment protocol, and long duration of follow-up.

A limitation of this trial is that the design is not that of a confirmatory trial. In addition, this trial will not use a placebo control group. However, evaluation of the remission and relapse rates, which are associated with the primary endpoint, will be performed by a pathological review board. The evaluation will be conducted under blind and independent conditions. Therefore, we believe that it will be possible to maintain objectivity and reduce potential bias.

We hope that the current study will increase the level of evidence on the effectiveness of an LNG-IUD in treating early EC and EHA. We hope that the LNG-IUD may be recognized as an effective alternative therapy for EC and EHA in obese women wishing for fertility preservation.

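### HOMA-IR is planned, but the schedule lists fasting glucose twice and no insulin; BMI and HOMA-IR are also confined to a subset selected on the primary endpoint

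*Protocol article*

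**What the plan says.** The Statistical analysis section lists, among its other analyses, "BMI values and homeostatic model assessment of insulin resistance (HOMA-IR) results of all response cases that wish to become pregnant". For two-group comparisons of continuous data it says that Student's "t-test or the Mann–Whitney U test will be used according to the normality assumption".

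Table 1 (Study assessments and procedures) has a row "FBG (fasting blood-glucose" and, further down, a row "Fasting blood sugar". Both are ticked at baseline and at 3, 6, 9, 12, 18 and 24 months. HbA1c, weight and BMI are ticked at the same visits. No row names insulin. The one open-ended draw, "Blood collection for biomarkers and genetic testing", is ticked at baseline only. The Baseline assessments section mentions "blood tests including tumor marker CA125" and does not name insulin.

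The Efficacy assessments section evaluates weight loss in the two groups and does not restrict this to responders. On metabolism, the Discussion says that "this trial will also evaluate the expected improvements in the metabolic profile following the addition of metformin". Both arms receive metformin (Randomization), and the Interventions section adds: "Because all participants in the trial will be obese, a weight loss program will be implemented".

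**The concern.** There are two problems and one wording point.

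- **Missing input.** HOMA-IR is the product of fasting insulin and fasting glucose, divided by a constant. A schedule with glucose twice and insulin nowhere does not supply it. An analysis plan cannot repair this afterwards: if insulin is not assayed and no suitable sample is kept, the value is lost.
- **Selected population.** Response is the primary endpoint and may differ by arm. The document itself links both sides to metabolism. The Introduction names obesity and insulin resistance as risk factors for the disease. The Discussion associates oral progestin with weight gain and diabetes, and says the LNG-IUD is not known to have systemic effects. Comparing arms among responders only can therefore distort the arm difference, and it discards women whose weight and BMI are already scheduled.
- **Wording.** The Discussion sentence can be taken as a promise to measure what metformin adds, which two metformin-containing arms cannot show.

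**Working it through.** **1. Schedule against analysis.**

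| HOMA-IR needs | Table 1 provides |
|---|---|
| Fasting glucose, baseline and follow-up | Two rows, same seven visits |
| Fasting insulin, baseline | Not named; at best part of the open-ended biomarker draw |
| Fasting insulin, follow-up | Nothing |

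Even if insulin were run on the baseline biomarker sample, there would be no follow-up value and so no change.

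**2. The plan's own sample size** (Sample size section: w = 0.3, two-sided alpha 0.05, power 0.80, 1:1). N = (1.960 + 0.842)² / 0.3² = 87.2, rounded up to 88 for equal arms; the noncentral chi-square power at 88 is 0.804. The stated 44 per arm reproduces. It is used below only as the starting number.

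**3. Size of the responder subset** (pCR rates from the Sample size section).
- 45% in both arms: 88 × 0.45 = 39.6, about 40.
- 68% for LNG-IUD and 60% for MA: 44 × 0.68 + 44 × 0.60 = 29.9 + 26.4 = 56.3, about 56.

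These are not upper bounds: the quoted interval reaches 86%, and 88 × 0.86 = 75.7. The wish to conceive reduces the count further by a share that the document does not give. Because every participant must wish to maintain fertility (Inclusion criteria), response is probably the main filter.

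**4. Detectable difference at 80% power**, in SD units: (1.960 + 0.842) × √(1/n₁ + 1/n₂).
- All randomised, 44 and 44: 0.60.
- 45% in both arms, 19.8 and 19.8: 0.89.
- 68% and 60%, 29.9 and 26.4: 0.75.
- If only half of the responders wish to conceive (assumption): 9.9 and 9.9 gives 1.26; 15.0 and 13.2 gives 1.06.

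**5. Possible selection bias** (illustrative). Suppose that the metabolic outcome has correlation r with an underlying tendency to respond, equal in both arms. The responder mean then shifts by r × φ(z_p)/p, where p is the pCR rate, z_p its normal quantile and φ the normal density. The factor φ(z_p)/p is 0.526 at 68%, 0.644 at 60% and 0.880 at 45%. For r from 0.2 to 0.5 (assumption):
- 68% against 60%: 0.118 × r = 0.02 to 0.06 SD.
- 45% against 60%: 0.236 × r = 0.05 to 0.12 SD.

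Under this simple model the bias is modest and the loss of precision is the larger cost. The model does not cover an arm-specific link between response and metabolism.

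**The case against.** **Table 1 is a summary with other gaps.** It has no renal or liver row although eligibility depends on creatinine and liver failure. The hysteroscopy and D&C row has no baseline tick although Baseline assessments requires the procedure. The ER/PR row is empty. A reader might infer that no HOMA-IR value will exist for any of the 88 women. The document does not support that: insulin may be measured and one row mislabelled. What stands is that the printed schedule and the analysis text conflict.

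**The subset item may be descriptive.** It does not name the two arms and sits next to the pregnancy outcomes, so it may be a pooled description of women about to attempt conception. The general sentence on two-group tests is not tied to it. This stands; the criticism applies to any arm comparison made in that subset.

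**Weight is already compared by group without restriction.** Height is taken only at baseline, so change in BMI is change in weight on a fixed scale. A reader might infer that all metabolic data are confined to responders; that is not so.

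**An unadjusted test is not an error.** Baseline adjustment is a gain in efficiency and can be left to an analysis plan. With a baseline to follow-up correlation of 0.5 to 0.9 (assumption), the gain over a change-score test is a factor 2/(1 + r), only 1.33 to 1.05. It is a preference here.

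**The metformin sentence is Discussion prose.** It speaks of improvement following metformin, is not a listed aim, and stands in a section that concedes the lack of a placebo group and the non-confirmatory design. To infer that the trial formally claims to estimate a metformin effect goes too far.

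**Conclusion.** The point holds in two limited parts. First, HOMA-IR is planned and, on the schedule as printed, cannot be calculated at follow-up; this is a conflict within the article and not a detail left to another document. Second, BMI and HOMA-IR are assigned to a population defined after randomisation by the primary endpoint. That is about 40 to 56 of 88 women at the plan's anticipated rates, before the pregnancy-wish filter, and an arm comparison there would lack a randomised basis. The sizes rest on those pCR rates applying to the combined regimens, although the 68% and 60% are given for the progestin treatments alone.

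The metformin sentence is a secondary wording matter. Metformin is common to both arms and given alongside a weight-loss programme, so a before-after change mixes metformin, progestin, weight loss and time. The two-year metformin-free criterion gives a clean baseline but does not separate these.

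HOMA-IR is a supporting outcome, neither the primary endpoint nor a named secondary aim. The LNG-IUD against MA comparison of pCR is untouched.

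**What to change.** - In Table 1, replace the duplicate "Fasting blood sugar" row with fasting insulin, taken from the same draw as the fasting glucose at each visit. If insulin is already being measured, correct the label.
- Compare BMI and HOMA-IR between arms in all randomised women at visits up to 12 months, preferably adjusted for the baseline value. Month 12 is the natural limit because women without a complete response leave the trial then (Follow-up evaluations). The few who leave earlier, for progression or pregnancy, need a stated handling.
- Keep the responders who wish to conceive as a descriptive summary, and label it so.
- Reword the Discussion sentence to say that the trial compares metabolic change between two metformin-containing regimens.

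The cost is one added assay on blood already drawn (at most 7 × 88 = 616 determinations) and some text. No extra visit, sample or participant is needed. The assay change is the urgent part, since insulin that was neither measured nor stored may not be recoverable.

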**Fig. 1 Fig1:**
[figure not shown]
Trial design. pCR, pathological complete response

The trial will only include women with early-stage EC. The criteria for early-stage EC are: (1) stage 1 disease (absence of lymphadenopathy or pelvic masses); (2) endometrioid cell type and International Federation of Obstetrics and Gynecology (FIGO) grade 1 disease; (3) no evidence of lymph vascular space invasion on examination of curettage specimens; (4) absent or only minimal myometrial invasion (depth of infiltration < 1/2 muscle thickness on magnetic resonance imaging [MRI] to exclude deeply invasive cancers); (5) serum cancer antigen (CA)125 level ≤ 30 U/mL [31].

Through strict patient inclusion criteria, we expect to control the probability of disease progression in trial patients at 3%. All patients will receive examinations and laboratory and imaging studies at baseline and 3, 6, 9, 12, 18, and 24 months after starting treatment.

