### Efficacy assessments

Assessments of effectiveness will be performed at 3, 6, 9, 12, 18, and 24 months after beginning treatment, including weight loss, histological examination of endometrial tissue specimens, and pregnancy outcomes. The total study duration will be 2 years.Weight loss of patients in the 2 groups will be evaluated.Hysteroscopic endometrial curettage will be performed to rule out disease progression (Fig. 2).Complete pathological response is defined as 2 consecutive negative endometrial biopsies. Endometrial tissue for pathological examination will be obtained during hysteroscopy. Tissue pathological examination will be performed in a double-blind manner by 2 senior pathologists. A third pathologist will be consulted if the results are inconsistent.A.If the disease progresses, such as atypical hyperplasia to endometrial cancer, well-differentiated adenocarcinoma of the endometrial to moderately or poorly differentiated endometrial cancer, or other types of endometrial cancer, hysterectomy will be recommended.B.If complete remission is achieved (2 consecutive negative endometrial biopsies), the patient will be recommended to remove the LNG-IUD or discontinue oral progesterone. Patients will continue to take metformin and monitor ovulation if pregnancy is desired. Participants who are not pregnant will be followed-up every 3 months for endometrial biopsy. Patients with a successful pregnancy and delivery who desire to retain reproductive function will undergo regular endometrial biopsies and imaging studies.C.If there is no response to treatment, but no progression or partial response, the current treatment will be continued; assessments and efficacy evaluations will be performed every 3 months. If there is progression or recurrence after remission, the patient will be recommended to terminate participation in the trial. If the assessments continue to indicate no response or partial response, assessments will be continued every 3 months for 12 months. If assessment at 12 months indicates an incomplete response, the patient will be recommended to terminate participation in the trial.D.If EC develops during follow-up after a complete response, it will be considered a recurrence and surgical treatment will be recommended.E.If there is no improvement or partial response after 12 months of treatment, the patient will be informed of the risks of continuing conservative treatment and a hysterectomy will be recommended.Pregnancy assessment: outcomes of abortion, premature delivery, and full-term delivery will be recorded.

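### Continuous secondary outcomes: a normality pre-test decides whether means or ranks are compared, and the stated two-group tests leave collected baseline values unused

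*Protocol article*

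**What the plan says.** The rule is in the Statistical analysis section of the protocol article. First, "The Kolmogorov–Smirnov normality test will be used to check the normality of continuous variables". Then, for two groups, "Student’s t-test or the Mann–Whitney U test will be used according to the normality assumption". The descriptive summary follows the same logic: mean and SD or median and IQR are reported "based on if the data are continuous or categorical and on the normality assumption". No covariate is named for the comparison between arms.

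A later paragraph opens with "This study will also investigate changes in the expression of molecular biomarkers" and says that "statistical tests of dependent data, such as the paired t-test or mixed-design ANOVA will be used". Repeated-measures methods are therefore planned, but in a paragraph about molecular biomarkers.

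On data collection, the Design section says "All patients will receive examinations and laboratory and imaging studies at baseline and 3, 6, 9, 12, 18, and 24 months after starting treatment". Table 1 lists weight, BMI, fasting glucose and HbA1c at baseline and at all six follow-up visits. It lists neither insulin nor HOMA-IR. Efficacy assessments adds "Weight loss of patients in the 2 groups will be evaluated". Statistical analysis lists BMI and HOMA-IR for responders who wish to become pregnant.

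**The concern.** A t-test compares means and a Mann–Whitney test compares ranks. When a test on the same data decides which is used, the observed distribution decides what is estimated. With six follow-up visits, one outcome could be reported as a difference in means at one visit and as a rank comparison at the next.

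Both tests as stated are also unadjusted. For outcomes measured on every patient before treatment, that discards information already paid for. The Discussion says the trial will evaluate improvement in the metabolic profile, and weight loss is one of the effectiveness assessments. The sample size was not set for either, so precision on them depends on the analysis.

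**Working it through.** **Inputs.** Sample size section: 44 per arm, 88 in total, w = 0.3, two-sided alpha 0.05, power 0.80. Statistical analysis: the selection rule above. The article gives no SD, no correlation r between baseline and follow-up, and no distribution shape, so every such value below is an assumption.

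**1. The plan's own figure.** N = (1.960 + 0.842)² / 0.3² = 7.849 / 0.09 = 87.2, so 88. The noncentral chi-square gives power 0.8035 at N = 88 and 0.7991 at N = 87. The figure reproduces, and it sizes a binary comparison only.

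**2. How the pre-test behaves.** Simulation with 44 per arm, both arms from one distribution, Mann–Whitney used if either arm has pre-test p < 0.05. The article does not say whether the Kolmogorov–Smirnov test is corrected for estimated mean and SD (Lilliefors), so both versions are shown.

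| Distribution | Mann–Whitney chosen, Lilliefors | Mann–Whitney chosen, uncorrected | Type I error of the two-stage rule (Lilliefors) |
|---|---|---|---|
| Normal | 10% | 0.05% | 0.050 |
| Lognormal, log-SD 0.3 | 51% | 1.8% | 0.054 |
| Lognormal, log-SD 0.5 | 88% | 16% | 0.051 |
| Lognormal, log-SD 0.8 | 99.7% | 70% | 0.052 |

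(6000 runs for the Lilliefors and type I error columns, 2000 for the uncorrected test.) The choice depends heavily on the version used. With mild skew the corrected version is close to a coin toss.

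**3. Whether the choice matters.** With equal means but unequal spread (lognormal, log-SD 0.3 v 0.8), the t-test rejects in 7% of trials, Mann–Whitney in 52% and the two-stage rule in 51%. The two tests answer different questions.

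**4. What the pre-test costs in power.** Assumed: lognormal, log-SD 0.6, true ratio 0.75, r = 0.6, 44 per arm, uncorrected pre-test. Power is 55–56% for the planned rule, 52% for always t, 57–58% for always Mann–Whitney, 59% for an unadjusted t-test on the log scale, and 78% for a log-scale model with the baseline value. The pre-test costs about 2 points against always Mann–Whitney. With the Lilliefors version the rule and always Mann–Whitney both reach 59%. Of the rise to 78%, about 78 − 59 = 19 points come from the baseline.

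**5. What the baseline is worth.** With SD σ at both times and n per arm, the variance of the arm difference is:
- follow-up value: 2σ²/n
- change score: 2(1 − r) × 2σ²/n
- ANCOVA: (1 − r²) × 2σ²/n

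The ANCOVA ratios are thus 1 − r² against the follow-up value and (1 − r²)/[2(1 − r)] = (1 + r)/2 against the change score. The smallest difference detectable with 80% power is 2.802 × √(2/44) = 0.60 SD unadjusted, multiplied by √(1 − r²) for ANCOVA. Unadjusted power for a 0.5 SD difference is 0.65.

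| r | Variance ratio v follow-up value | 88 patients worth about | Power for 0.5 SD | Smallest detectable (SD) | Variance ratio v change score |
|---|---|---|---|---|---|
| 0.3 | 0.91 | 97 | 0.69 | 0.57 | 0.65 |
| 0.5 | 0.75 | 117 | 0.77 | 0.52 | 0.75 |
| 0.7 | 0.51 | 173 | 0.91 | 0.43 | 0.85 |
| 0.8 | 0.36 | 244 | 0.97 | 0.36 | 0.90 |

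Simulated ANCOVA power at r = 0.5, 0.7 and 0.8 was 0.76, 0.90 and 0.97, in agreement.

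**6. Weight as an example.** Assumed SD 15 kg and r = 0.9. The 95% half-widths are:
- weight at a visit: 1.96 × 15 × √(2/44) = 6.27 kg
- weight change: 6.27 × √0.2 = 2.80 kg
- ANCOVA: 6.27 × √0.19 = 2.73 kg

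Against the change score, the gain in standard error is 1 − 2.73/2.80 = 2.5%.

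**The case against.** The strongest reply is that little is at stake. The two-stage rule holds its type I error, costs about 2 power points, and touches no categorical endpoint in a trial that calls itself non-confirmatory. Naming no covariate is silence in a condensed article, and an unseen analysis plan may supply one. All of this limits the size of the point. It does not remove it, because the article goes beyond silence: it names the selection rule and the two tests.

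Four stronger readings are tempting, and the documents do not support them.
- A reader might infer that the pre-test almost never rejects normality and so does nothing. That holds mainly for mild skew and an uncorrected test, and the article does not say which version applies. If it were so, the t-test would nearly always be used and the measure would seldom switch.
- A reader might infer that baseline is ignored throughout. Weight loss is itself a change from baseline, and paired or mixed-design tests are planned for molecular biomarkers.
- A reader might infer that adjustment would more than halve the interval for weight, from 6.3 to 2.7 kg. The article names weight loss as the outcome, so the fair comparison is 2.80 with 2.73 kg.
- A reader might apply 44 per arm to BMI and HOMA-IR as listed in Statistical analysis. Those are for responders wishing pregnancy, a subset formed after randomisation, and baseline adjustment would not make that a randomised comparison.

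**Conclusion.** The point holds for continuous secondary outcomes and should be acted on, though it threatens no main conclusion. The stated rule lets the data choose between means and ranks, and the stated two-group tests use no baseline covariate. The loss is mainly one of precision: 9% to 64% of the variance for r from 0.3 to 0.8 where follow-up values are compared, and 35% to 10% over the same range where change scores are compared. For weight loss with r near 0.9 the gain is slight.

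These sizes rest on assumed r, SD and skew and on 44 evaluable patients per arm. The last is an upper limit, because Follow-up evaluations withdraws patients with progression at any visit and those without complete response at 12 months. Validity of the p-values is not in question. The pCR, pregnancy and recurrence analyses and N = 88 are unchanged.

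**What to change.** - Delete the normality pre-test as the rule for choosing tests and summaries.
- For weight, BMI, fasting glucose and HbA1c in all randomised patients, pre-specify one effect measure each, with a log scale fixed in advance where skew is expected.
- Analyse by ANCOVA at a named visit, or by a mixed model with arm, visit and the baseline value. Report the adjusted difference with its 95% CI.
- Keep a rank test as a named sensitivity analysis.
- Apply the same model to HOMA-IR only if it is measured at baseline, since Table 1 lists neither it nor insulin.
- Label the BMI and HOMA-IR results in responders wishing pregnancy as descriptive.

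The cost is a revision of the analysis text. For the four named outcomes no extra data are needed, because Table 1 already collects them at baseline and at every follow-up visit.
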